##### Mobile Affect Regulation Intervention With the Goal of Lowering Depression Intervention Content

The resulting MARIGOLD intervention teaches eight positive emotion skills using lessons and homework that have been tailored to people with elevated symptoms of depression (see Table 1).

**Table 1 table1:** Mobile Affect Regulation Intervention with the Goal of Lowering Depression (MARIGOLD) intervention content adapted for depression.

Session		MARIGOLD^a^ intervention content
**Session 1**		
	Skills 1 and 2: noticing and amplifying positive events; Skill 3: gratitude	Learning to notice small positive moments in life and savoring or amplifying the positive emotional experience. Noticing positive events can help to reduce stress, even in the face of significant life stress Cultivating gratitude as another way to savor positive moments. The potential for gratitude to strengthen our connections with others
	Depression material	Recognizing cognitive biases that can lead to discounting or failing to notice or remember positive events
	Exercises	Daily positive events journal. Daily gratitude journal
**Session 2**		
	Skill 4: activation	Techniques for setting goals that are appropriately challenging but feasible
	Depression material	Ways to practice scheduling activities to break out of a negative spiral Added emphasis on setting small, attainable goals and working up to challenging goals gradually How to select goals that will provide pleasure or mastery experiences
	Exercises	Select a goal for the week and record progress daily
**Session 3**		
	Skill 5: mindfulness	Learning to increase the enjoyment of everyday activities by training ourselves to pay attention, on purpose, in the present moment, with nonjudgment. Learning to practice mindfulness both informally and formally
	Depression material	Using present-focused awareness to combat rumination. Using acceptance to tolerate unpleasant situations with less negative emotion
	Exercises	Select an everyday activity to do mindfully (informal practice). Guided mindfulness meditations (formal practice)
**Session 4**		
	Skill 6: positive reappraisal; Skill 7: strengths	Positive reappraisal as a way to respond to everyday stressors and dispute excessively negative interpretations. Recognizing that it is possible to acknowledge a situation as negative but still appreciate potential benefits (silver linings) or mitigating factors Recognizing personal strengths, skills, or talents
	Depression material	Role of negative cognitions in causing or maintaining depression. Support for acknowledging strengths even in the presence of low self-esteem
	Exercises	Daily reappraisal journal Daily strengths journal (record ways a personal strength or talent was used)
**Session 5**		
	Skill 8: acts of kindness	Engaging in small acts of kindness can help promote happiness and well-being for the individual, in addition to strengthening our relationships
	Depression material	Small, prosocial acts that can be performed even if one is relatively socially isolated
	Exercises	Do something nice for someone else each day and record it in a daily kindness journal

^a^MARIGOLD: Mobile Affect Regulation Intervention with the Goal of Lowering Depression.

The skills are (in the order that they are presented) as follows: (1) noticing positive events, (2) amplifying positive events, (3) gratitude, (4) behavioral activation, (5) mindfulness, (6) positive reappraisal, (7) personal strengths, and (8) acts of kindness. MARIGOLD is delivered as a self-paced, Web-based intervention arranged into five modules containing 1 to 3 skills each. Each module is designed to be completed within 1 week; however, to allow for variations in individual schedules and self-pacing, participants are given a total of 7 weeks to complete the MARIGOLD course. Participants must finish the current week’s skills before the next one’s become available, so the skills are taught in succession. Each skill is associated with a home practice exercise in a journal format, and participants are encouraged to spend approximately 10 min each day reviewing the skill and completing home practice. Participants may also revisit previous weeks’ skills and home practice exercises. After completion of the course, participants maintain access to the course website indefinitely, allowing them to review the skills or continue with their home practice.

In addition, booster sessions that contain brief summaries of the positive emotion skills, along with encouragement and goal setting for continued practice, become available immediately after course completion. For example, if participants are going through a booster session for skill # 8: acts of kindness, they will review a brief summary the skill, as well as a few examples of random acts of kindness. They will also have the chance to review their previous journal entries for the skill and print out a bonus handout on the skill. Finally, in the booster sessions, participants have the opportunity to set a goal to enact the skill. Specifically, participants will be asked to complete the following steps: (1) set a goal for enacting the skill (ie, “I will commit to doing something nice for a friend, loved one, or stranger every day”), (2) a time frame of the commitment (1 week, 2 weeks, 1 month, or 2 months), (3) the frequency of the commitment (more than once a day, once a day, every other day etc), (4) how they plan to keep track of their commitment (write about it on the MARIGOLD website or talk to a friend or activity partner), (5) write down an encouraging note to themselves for when it gets difficult to enact the skill, and (6) digitally sign their name to a summarized page with their commitment. Following these six steps, participants will be emailed a copy of their responses as a reminder.

### Outcomes

#### Retention and Adherence

In this study, we define retention as the number of assessment questionnaires that participants complete. In addition, we define adherence to the intervention in two ways: (1) the number of lesson modules accessed by the participant and (2) the proportion of the intervention content that participants complete (ie, the number of pages that participants view out of the total number of pages in the intervention).

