Web-based interventions that are supported by a trained professional (eg, having a trained professional associated with the study guide the participant through the intervention content via email or telephone) have been found in meta-analyses to produce larger effect sizes and better adherence relative to Web-based interventions that are self-guided [43,50]. For instance, one meta-analysis found that the average percentage of fully adherent participants (participants who completed all sessions in the intervention) was 26% for self-guided Web-based interventions versus 72% for supported interventions [50]. However, a disadvantage of supported interventions is that they tend to be more time-intensive, costly, and difficult to disseminate relative to self-guided interventions. This research aims to develop and test low-cost, resource-efficient, and scalable strategies for promoting adherence and retention in Web-based interventions.

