#### Retention and Adherence

Retention will be defined as completing the baseline, postintervention, and follow-up assessments. We will categorize retention at each assessment as a binary outcome and will test for differences in the proportions of participants who are retained at each assessment using a binary logistic regression model using dummy variables to represent each arm. Adherence will be assessed in intervention participants only and measured in two ways: (1) the number of skills accessed and (2) the proportion of the intervention completed (ie, the number of pages viewed out of the total possible pages across all lesson modules in the intervention). In the phase 1 pilot, we will report descriptive statistics of adherence in the intervention arm and will explore whether retention differs as a function of arm (intervention vs emotion-reporting control vs waitlist control) using a binary logistic regression, with dummy variables to represent each arm. In the phase 2 pilot, we will explore whether retention and adherence differ as a function of enhancement type using a binary logistic regression for retention and linear regressions for adherence, with dummy variables to represent each arm. In the phase 3 pilot, we will use additional contrast tests to explore whether retention and adherence differ as a function of enhancement type received (no enhancement, facilitator contact, virtual badges, or ODB), as well as whether receiving certain combinations of enhancements offers additional benefits for increasing retention and adherence.

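### Linear regression of a capped, gated adherence score needs unequal-variance standard errors, because arm-to-arm contrasts can otherwise be mis-sized in either direction

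*Protocol article*

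**What the plan says.** The Outcomes section (Retention and Adherence) defines adherence as (1) "the number of lesson modules accessed by the participant and (2) the proportion of the intervention content that participants complete", the second being pages viewed out of all pages. Planned Analyses describes the first measure differently: "Adherence will be assessed in intervention participants only and measured in two ways: (1) the number of skills accessed". The count therefore runs to 5 modules or to 8 skills, depending on the section. The course is "arranged into five modules containing 1 to 3 skills each" (3, 1, 1, 2 and 1 in Table 1). The text after Table 1 says that a week's skills must be finished before the next ones "become available, so the skills are taught in succession".

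For phase 2, Planned Analyses compares the arms "using a binary logistic regression for retention and linear regressions for adherence, with dummy variables to represent each arm". For phase 3 it says "we will use additional contrast tests to explore whether retention and adherence differ as a function of enhancement type received", and it also looks at combinations of enhancements. No variance estimator is named. The only completion rates in the article are in the Background: full adherence "was 26% for self-guided Web-based interventions versus 72% for supported interventions".

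**The concern.** A score that cannot exceed its maximum, on a course that must be taken in order, places each participant either at a stopping point along the way or at the ceiling. If one enhancement moves many people to the ceiling, the spread in its arms changes relative to the others. Ordinary regression with arm dummies gives every contrast the residual variance averaged over all arms. A contrast between two arms whose own variance lies above that average gets a standard error that is too small. A contrast between two arms below it gets one that is too large. The apparent evidence on the discussion board or badges would then depend partly on how well facilitator contact performed. This matters because testing the enhancements for retention and adherence is the second stated objective.

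**Working it through.** The article gives no alpha, standard deviation or effect size for adherence, so there is no figure of its own to reproduce.

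**Inputs from the article.** Phase 2 has 3 arms of 25. Phase 3 has about 67 per arm, with 8 intervention arms, 4 of them with facilitator contact (FC). Completion is 26% self-guided and 72% supported.

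**Assumptions.** Two-sided 5%; FC is the enhancement that works; a constant chance of going on at each module; completion of 26% without FC and 72% with it, then other values; a share *s* who never open module 1.

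**Variance of modules accessed (M).** Let *c* be overall completion and r = (c/(1−s))^(1/5). Then P(M ≥ k) = (1−s)·r^(k−1) for k = 1 to 5, E[M] = Σ P(M ≥ k) and E[M²] = Σ (2k−1)·P(M ≥ k).

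- c = 26%, s = 0: r = 0.764; the P(M ≥ k) are 1, 0.764, 0.583, 0.446, 0.340; mean 3.13; variance 12.39 − 9.82 = 2.57.
- c = 72%, s = 0: r = 0.936; the P(M ≥ k) are 1, 0.936, 0.877, 0.821, 0.769; mean 4.40; variance 20.86 − 19.39 = 1.47.

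**Size of a contrast between two equal arms.** Each arm has true variance v. The correct standard error is √(2v/n), and pooled regression uses √(2v̄/n), where v̄ is the average variance over arms. With R = √(v̄/v), the rejection rate is about 2[1 − Φ(1.96R)].

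- Phase 3: v̄ = (2.57 + 1.47)/2 = 2.02. Without FC, R = √(2.02/2.57) = 0.887, giving 8.2%. With FC, R = √(2.02/1.47) = 1.172, giving 2.2%.
- Phase 2, board versus badges: v̄ = (2 × 2.57 + 1.47)/3 = 2.20, R = 0.926, giving 7.0%.

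Simulation agrees: 8.1% to 8.5% and 2.0% to 2.4% in phase 3, and 6.9% to 7.2% in phase 2. Scoring skills instead of modules gives much the same.

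**Sensitivity (same formulas, modules).**

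| Completion, no FC / FC | Never start, no FC / FC | Variance, no FC / FC | Phase 3, arms without FC | Phase 3, arms with FC | Phase 2, board vs badges |
|---|---|---|---|---|---|
| 26% / 72% | 0 / 0 | 2.57 / 1.47 | 8.2% | 2.2% | 7.0% |
| 26% / 72% | 10% / 10% | 3.27 / 2.88 | 5.7% | 4.3% | 5.5% |
| 26% / 72% | 20% / 20% | 3.86 / 4.14 | 4.6% | 5.4% | 4.7% |
| 26% / 72% | 20% / 10% | 3.86 / 2.88 | 6.7% | 3.4% | 6.1% |
| 26% / 72% | 30% / 20% | 4.34 / 4.14 | 5.3% | 4.7% | 5.2% |
| 26% / 50% | 0 / 0 | 2.57 / 2.27 | 5.7% | 4.3% | 5.5% |
| 50% / 85% | 0 / 0 | 2.27 / 0.84 | 10.5% | 0.8% | 8.2% |

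If all arms complete equally, v̄ = v and the test is correct.

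**Balanced main effect in phase 3.** For board yes versus no, averaged over the other two factors, the true variance is Σvⱼ/(16n) = 8v̄/(16n) = v̄/(2n). That is exactly what the pooled formula uses, so with equal arm sizes there is no distortion. Simulated rates were 4.5% to 5.4%.

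**With the change.** HC3 or separate variances gave 4.7% to 5.4% in the simulated scenarios.

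**The case against.** The strongest objection is that the article never says a pooled variance will be used. Linear regression with arm dummies is compatible with robust errors, and that choice is often left to an analysis plan, which is not shown here. This stands as a limit: the pooled variance is the default meaning of the stated method, not a stated choice. The point survives as a qualifier that the named method needs for this particular outcome.

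Second, the size rests on assumptions. The analyses are intention-to-treat and no minimum of one module is set, so zeros are possible, and a modest share of them removes the effect or turns it round. The 72% comes from interventions in which a professional guides the participant. Facilitator contact here is capped at 5 minutes a week without counseling, so its effect on completion may be smaller. Both points stand. In the other direction, the run-in screens out noncompliant people, so completion could also be higher than assumed.

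Third, linear regression is named for phase 2 only, the comparisons are described as exploratory, and the exact phase 3 contrasts are not fixed. This stands too. Phase 2 is not factorial, however, so it lacks the protection of balanced main effects, and the phase 3 interest in a no-enhancement category and in combinations invites contrasts between single arms.

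A reader might infer three stronger things that the document does not support. Higher completion does not always mean smaller spread: with 20% never-starters in every arm, the variance is larger at 72% than at 26%. Tests of the other enhancements are not all wrong, because balanced main effects hold. Nor does the article state any rule by which the board or badges would be kept or dropped on these tests.

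**Conclusion.** The concern holds in a limited form. Adherence is a bounded, gated score analysed by linear regression, and under ordinary pooled-variance errors single-arm contrasts can be too liberal or too conservative. At 26% versus 72% completion with everyone starting, the error is about 8% or 2% in phase 3 and about 7% in phase 2, against a nominal 5%. It reaches about 10% at 50% versus 85%. It is close to 5% if 10% of every arm never start, if completion differs only as 26% versus 50%, or if arms adhere alike. The direction cannot be known in advance, because it depends on how non-completers drop out. The mean differences themselves are unaffected, and bounded scores do not by themselves rule out a linear model.

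**What to change.** Add one sentence to the adherence analysis for phases 2 and 3: the linear model and its mean differences are kept, and all adherence tests and confidence intervals use heteroscedasticity-consistent (HC3) or arm-specific variances. No new data are needed and no estimate changes. The only cost is very slightly wider intervals if the variances prove equal. The article reports that data collection is complete and analysis under way, so the report should say when this choice was made. A logistic analysis of finishing the whole course would be an optional extra and is not part of the correction. The same edit should settle whether the count is of modules or of skills, since the two sections differ.

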#### Preliminary Efficacy Measures

Assessments include self-report measures of demographic and clinical characteristics, depression, positive and negative emotion, psychological well-being, coping resources, potential moderators, and satisfaction with the intervention. See Multimedia Appendix 1 for the full list of measures. The follow-up interviews in phases 1 and 2 are conducted over the telephone by research staff; if the participant is in the facilitator contact arm (phase 2 only), we ensure that the research staff conducting the follow-up interview is not the same person who was assigned as the participant’s facilitator. In phase 3, the follow-up interviews are delivered as a Web-based survey.

The primary efficacy outcome in the proposed research is depressive symptom severity, which we are measuring using the PHQ-8 [55]. We will also assess the Center for Epidemiological Studies-Depression [63] as an additional measure of depressive symptomatology. Emotion is also a central construct in the proposed research. As such, we are measuring it multiple ways: (1) daily emotion reports [35], completed daily during the run-in period (which serves as the baseline measure) and during the 5- to 7-week intervention period, and also daily, in 1-week bursts at each of the three postintervention assessment periods (post intervention, FU1, and FU2); (2) past-week emotion reports [35] at each of the four assessment periods (baseline, post intervention, FU1, and FU2); and (3) EMA [56] completed three times per day for 3 days per week during the run-in period (which serves as the baseline measure) and for 1-week bursts at each subsequent assessment (post intervention, FU1, FU2).

### Study Design

#### Phase 1: Pilot Test of the Web-Based Positive Emotion Skills Intervention Tailored for Participants With Elevated Symptoms of Depression

Participants (N=60) are randomized into one of three arms: (1) MARIGOLD intervention (N=30), (2) active control (daily emotion reporting during the 5-week intervention period; N=15), or (3) waitlist control (N=15). Participants in the intervention arm receive a five-session positive emotion skills intervention tailored for participants with elevated symptoms of depression (described above). Participants in the daily emotion reporting arm complete the DES [35] daily for the 7-week duration of the intervention period. In past research, we have established that emotion reporting is acceptable as a control condition (retention rates of approximately 80%, similar to the intervention) and that participants perceive it as being beneficial, providing some of the features of a placebo control [53]. Participants in the waitlist control group only complete the assessment questionnaires. Upon completion of the FU1 assessment, participants in both the emotion-reporting and waitlist control arms receive access to the MARIGOLD intervention. Following phase 1, we review the study feedback from telephone interview transcripts and modify and refine the study design, staff training, and intervention content accordingly.

#### Phase 2: Pilot Test of Three Enhancements to Increase Retention and Adherence

In phase 2, we are developing and pilot testing three enhancements that can be added to the Web-based intervention for the purpose of boosting retention and adherence among people with elevated depressive symptoms. Participants (N=75) are randomized into one of three arms, the intervention plus one enhancement: (1) intervention + facilitator contact (N=25), (2) intervention + ODB (N=25), and (3) intervention + virtual badges (N=25). Each enhancement is designed to improve retention and adherence to the intervention by removing practical and motivational barriers to continued engagement. We describe each enhancement strategy below.

##### Facilitator Contact

Even when interventions are entirely computerized, contact with a person associated with the intervention has been found to increase adherence to the study [43,85-89]. Participants assigned to this enhancement arm are contacted once per week by a facilitator, who encourages them to continue with the program and answers any questions they have about the study. Contact is limited to no more than 5 min per week. The facilitator schedules a time each week to call the participant by telephone. If they cannot agree on a time or the participant cannot be reached that week, the facilitator contacts the participant by email. The content of the facilitator script is similar for both telephone and email communication. Before contacting the participant (either via telephone or email), the facilitator checks in on the participant’s progress in the course (eg, the skills accessed that week, home practice completion, and daily emotion survey completion). The facilitator begins the facilitator contact (both telephone and email) by briefly summarizing to the participant their progress in the course that week. Next, facilitators check in with the participant about (1) the skills covered that week, (2) the home practice that week, (3) the daily emotion surveys, and (4) any issues with the technology. Specifically, the facilitator asks participants how each component (eg, skills covered and home practice) went that week, whether the participant experienced any challenges, difficulties, or barriers with each component that week, and whether they had any comments or questions. The facilitator contact ends with the facilitator confirming the time for next week’s facilitator contact call, unless it’s the final week (week 7). When facilitators email participants, facilitators encourage participants to reply with questions, comments, and technology issues. The facilitator does not offer counseling to the participant during the facilitator contact. If the participant begins to request counseling, the facilitator reminds the participant that the facilitator is not in the position to provide advice or therapy to the participant and reinforces that their role is to answer questions, help the participant progress through the course, and discuss challenges, goals, or technology issues. The facilitator encourages the participant to identify opportunities to apply the MARIGOLD skills in their daily life using language from the course content. In cases where the participant is actively seeking counseling, the facilitator recommends that the participant speak with their medical provider, and if they don’t have a medical provider, the facilitator offers resources for the participant to find medical coverage (see training section below).

##### Online Discussion Board

Prior research has found that receiving peer support from other users via a Web-based discussion forum can increase rates of adherence to Web-based interventions [90-94]. Participants assigned to this enhancement arm are able to share questions, experiences, and encouragement with other participants in a pseudonymous Web-based environment (ie, each participant has a consistent username, but it contains no information about their identity). Research assistants serve as moderators, checking the discussion board one or more times weekly to remove posts that are inappropriate (eg, profanity, advertisements, and bullying), to identify any concerns about participant safety or suicidality, to post prompts or suggestions to start discussions, to provide encouragement, and to answer broad questions about the study. Moderators remind users regularly and as needed about guidelines for the discussion board (eg, its supportive purpose and the importance of protecting privacy). They do not provide detailed answers to questions about the intervention or discuss individual exercise responses.

